## 1.2 Schema

**Figure 1-1 Study Design for Phase 1**

[figure not shown]

**Figure 1-2 Study Design for Phase 2**

**Phase 2**

[figure not shown]

Other Solid Tumor  
Arm B (single agent)  
n = ~70

[figure not shown][figure not shown][figure not shown]

CRC  
Arm F (combination)  
n = ~40

CRC: colorectal cancer [REDACTED]

Arm B: solid tumors other than NSCLC treated with D-1553 single agent

Arm F: CRC treated with D-1553 at combination RP2D with cetuximab

### 1.3 Schedule of Visits and Procedures

**Table 1-1 Schedule of Activities for Phase 1a (Dose Escalation)**

| Procedures                                                                                        | Day
Visit Window | Screening
(up to 28 days before
Day 1) |                       | Intervention Period                           |   |     |                        | End of
Treatment or
Withdrawal  | Follow-up                              |           |
|---------------------------------------------------------------------------------------------------|---------------------|----------------------------------------------|-----------------------|-----------------------------------------------|---|-----|------------------------|----------------------------------------------------|----------------------------------------|-----------|
|                                                                                                   |                     | -28 to -1                                    | -1 to 1  | Treatment Cycle 1
(21-day treatment cycle) |   |     | ≥ Treatment
Cycle 2 |                                                    | Safety
(30 days after
last dose) | PFS       |
|                                                                                                   |                     |                                              |                       | 1                                             | 2 | 14  | 1                      |                                                    |                                        |           |
|                                                                                                   |                     | NA                                           | NA                    | 0                                             | 0 | ± 4 | ± 4                    | + 7                                                | ± 7                                    | ± 2 weeks |
| Informed consent                                                                      |                     | X                                            |                       |                                               |   |     |                        |                                                    |                                        |           |
| Medical history                                                                       |                     | X                                            |                       |                                               |   |     |                        |                                                    |                                        |           |
| Diagnosis and history of solid tumor                                                  |                     | X                                            |                       |                                               |   |     |                        |                                                    |                                        |           |
| Demographics                                                                          |                     | X                                            |                       |                                               |   |     |                        |                                                    |                                        |           |
| Physical examination                                                                  |                     | X                                            | X                     |                                               |   | X   | X                      | X                                                  |                                        |           |
| Inclusion and exclusion criteria                                                      |                     | X                                            | X                     |                                               |   |     |                        |                                                    |                                        |           |
| Pregnancy test  (WOCBP only)                                                          |                     | X                                            | X                     |                                               |   |     | X                      | X                                                  |                                        |           |
| ECOG performance status                                                               |                     | X                                            |                       | X                                             |   |     | X                      | X                                                  |                                        |           |
| Assessment of KRAS G12C status                                             |                     | X                                            |                       |                                               |   |     |                        |                                                    |                                        |           |
| Vital signs                                                                          |                     | X                                            | X                     | X                                             | X | X   | X                      | X                                                  |                                        |           |
| Laboratory assessments 
(hematology, blood chemistry,
urinalysis, coagulation) |                     | X                                            | X                     |                                               |   | X   | X                      | X                                                  |                                        |           |
| 12-lead ECG                                                                          |                     | X                                            |                       | X                                             |   | X   | X                      | X                                                  |                                        |           |
| ██████████ ██████████                                                                             |                     | X                                            |                       |                                               |   |     | X                      | X                                                  |                                        |           |
| ██████ ██████                                                                                     |                     | X                                            | X                     |                                               |   |     | X                      | X                                                  |                                        |           |
| D-1553                                                                               |                     |                                              |                       | X                                             | X | X   | X                      |                                                    |                                        |           |

| Procedures                                   | Day
Visit Window | Screening
(up to 28 days before
Day 1) |                       | Intervention Period                           |   |     |                        | End
of
Treatment or
Withdrawal  | Follow-up                              |                 |
|----------------------------------------------|---------------------|----------------------------------------------|-----------------------|-----------------------------------------------|---|-----|------------------------|-------------------------------------------------------|----------------------------------------|-----------------|
|                                              |                     |                                              |                       | Treatment Cycle 1
(21-day treatment cycle) |   |     | ≥ Treatment
Cycle 2 |                                                       | Safety
(30 days after
last dose) | PFS             |
|                                              |                     | -28 to -1                                    | -1 to 1  | 1                                             | 2 | 14  | 1                      |                                                       |                                        |                 |
|                                              |                     | NA                                           | NA                    | 0                                             | 0 | ± 4 | ± 4                    | + 7                                                   | ± 7                                    | ± 2 weeks       |
| Blood sample collection for PK  |                     |                                              |                       | X                                             | X | X   | X                      |                                                       |                                        |                 |
| Tumor assessment                |                     | X                                            |                       |                                               |   |     | X                      | X                                                     |                                        | X  |
| AE/SAE review                                |                     |                                              | X                     | X                                             | X | X   | X                      | X                                                     | X                                      |                 |
| Prior/concomitant medication
review       |                     | X                                            | X                     | X                                             | X | X   | X                      | X                                                     | X                                      |                 |

AE: adverse event; ALT: alanine aminotransferase; ALP: alkaline phosphatase; AST: aspartate aminotransferase; BUN: blood urea nitrogen; CNS: central nervous system; CRC: colorectal cancer; CT: computerized tomography; ECG: electrocardiogram; ECOG: Eastern Cooperative Oncology Group; INR: international normalized ratio; GGT: gamma-glutamyl transferase; LDH: lactate dehydrogenase; MRI: magnetic resonance imaging; NSCLC: non-small cell lung cancer; PK: pharmacokinetic(s); aPTT: activated partial thromboplastin time; RBC: red blood cell; RDE: recommended dose for expansion; SAE: serious adverse event, WBC: white blood cell; WOCBP: women of childbearing potential

1. Written informed consent should be obtained prior to any screening procedure or study procedure.
2. Medical history includes details of oncology history, smoke history, history of other diseases (active or resolved) and concomitant illnesses; should be collected within 28 days prior to first dose of study intervention.
3. History of solid tumor information must include previous treatment history and mutation information, if available.
4. Demographic data includes age, sex and race/ethnic group as indicated by the subject.
5. Physical examination includes major body systems. Body weight will be recorded at screening and Day 1 of each treatment cycle. Height will only be measured at Screening.
6. Inclusion and exclusion criteria must be evaluated prior to first dose of study intervention.
7. Serum or urine pregnancy tests will be performed at Screening, Pre-Dose Day -1 and End of Treatment or Withdrawal as well as on Day 1 of every odd-numbered cycle (except Cycle 1). Subjects with a positive pregnancy test will be permanently discontinued from treatment with study intervention and will enter into a safety follow-up period.
8. ECOG performance status grade is available in [Appendix 1](#) of the protocol.

9. KRASG12C mutation status must be documented for the purpose of the inclusion criteria using a blood or tumor tissue sample and can be from a previously conducted local laboratory test result up to 5 years prior to this study. The method used for the test should also be collected.
10. Vital signs include body temperature, pulse, respiratory rate and blood pressure. These should be done once pre-dose and once post-dose on dosing days, and once on non-dosing days (pre- and post-dose procedures in BID cohort will only be required for the first dose during the day). Both pre-dose and post-dose measurements can have 1-hour window.
11. Laboratory assessments includes hematology, blood chemistry, urinalysis and coagulation. Weekly or more frequent tests may be given at the investigator's discretion:  
Hematology includes complete blood count including RBC, hemoglobin, hematocrit, WBC and differential (neutrophils, eosinophils, basophils, lymphocytes, monocytes and other cells) and platelet count. Blood chemistry includes total, direct and indirect bilirubin, ALT, AST, ALP, LDH, total protein, albumin, sodium, potassium, magnesium, chloride, calcium, phosphorus, BUN, creatinine, uric acid, glucose. Additional blood chemistry tests may be performed as clinically indicated (e.g., amylase, lipase, creatinine kinase, GGT). Urinalysis includes pH, specific gravity, protein, glucose, ketones, RBC, WBC, bilirubin. Additional analyses may be required as clinically indicated. Coagulation parameters should be determined throughout the study when clinically indicated, including aPTT and INR.
12. Triplicate measurements of 12-lead ECGs (recommended to perform 3 ECGs within 5 minutes) will be recorded during screening, at end of treatment, and at 2~6 hours post-dose on indicated study days and read by the central laboratory (pre- and post-dose procedures in BID cohort will only be required for the first dose during the day). The time of post-dose ECG is recommended to be as close as possible to the PK sampling time unless it's too difficult for clinical practice.
13. [REDACTED]  
[REDACTED]  
[REDACTED]
14. Each subject will receive daily oral doses of D-1553 (once daily for Cohorts 1 to 4 and twice daily for Cohorts 5 to 7) from Day 1 to Day 21 on an empty stomach (no food and drink, except for water, for at least 0.5 hours before and after dosing). Each 21day period will be considered as 1 treatment cycle. Subjects in the twice daily administered cohorts will be dosed with study intervention approximately 12 ( $\pm$  3) hours apart. D-1553 will be dispensed on Day 1 of each cycle together with the instruction of taking the drug at home and the diary for recording of dose taken.
15. Blood samples will be collected for PK analysis of D-1553 at the following timepoints: pre-dose, 1 hour, 2 hours, 4 hours, 6 hours and 10 hours post-dose on Day 1 of treatment cycle 1, Day 14 of treatment cycle 1, and Day 1 of treatment cycle 3; pre-dose on Day 2 of treatment cycle 1.

16. Radiologic imaging will be used for tumor assessment. A CT scan (with or without contrast) of the chest, abdomen and pelvis will be performed to assess metastatic disease. A bone scan will be performed in the event of clinical symptoms of bone metastases. A baseline brain MRI (with or without contrast; CT is acceptable if MRI is contradicted), should be performed for subjects with a history of or suspected to have CNS metastases. For subjects with no CNS metastases at baseline, it is not necessary to repeat brain MRI unless CNS involvement is suspected during the study. Screening scans can be performed within 6 weeks prior to Day 1 of treatment cycle 1. Tumor assessment will be performed during screening and at the completion of every 2 treatment cycles for the first 8 treatment cycles, thereafter at the end of every 3 treatment cycles until disease progression, start of new anticancer treatment, death, withdrawal of consent, or until end of study. There is a  $\pm 7$ -day window for each tumor assessment. For PFS, subjects who do not have disease progression on study will be followed for tumor assessment, approximately every 12 weeks ( $\pm 2$  weeks), until disease progression, death, lost to follow-up, start of another anticancer therapy, or other reasons that a follow-up is not possible.
17. These procedures can be done on Day -1 or Day 1 but have to be completed prior to first dose of study intervention. They are intended for checking the subject status before the first dose, not for eligibility. A subject's eligibility should be determined during the screening period. Laboratory tests performed in the screening period within 7 days of Day 1 do not need to be repeated on Day -1 or Day 1 unless clinically indicated.
18. These visits need to be completed within 7 days of the last dose of study intervention:
  - a. Subjects who stop treatment due to disease progression at the visit time do not need to repeat the imaging examination;
  - b. The radiologic imaging examination needs to be repeated if more than 4 weeks have passed from the last examination to the end of treatment visit;
  - c. Other examinations are required to be repeated if more than 1 week from last examinations.
19. [REDACTED]

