18. These procedures can be done on Day -1 or Day 1 but have to be completed prior to first dose of study intervention. They are intended for checking the subject status before the first dose, not for eligibility. A subject's eligibility should be determined during the screening period. Laboratory tests performed in the screening period within 7 days of Day 1 do not need to be repeated on Day -1 or Day 1 unless clinically indicated.
19. These visits need to be completed within 7 days of the last dose of study intervention:
  - a. Subjects who stop treatment due to disease progression at the visit time do not need to repeat the imaging examination;
  - b. The radiologic imaging examination needs to be repeated if more than 4 weeks have passed from the last examination to the end of treatment visit;
  - c. Other examinations are required to be repeated if more than 1 week from last examinations.
20. A follow-up phone call is allowed to perform the check on AE status and concomitant medications.
21. Subjects who do not have disease progression on study will be followed for tumor assessment, approximately every 12 weeks ( $\pm 2$  weeks), until disease progression, death, lost to follow-up, start of another anticancer therapy, or other reasons that a follow-up is not possible.
22. Subjects will be followed for survival status monthly ( $\pm 2$  weeks), until death, lost to follow-up or other reasons that a follow-up is not possible. The follow-up can be done via telephone call.
23. [REDACTED]
24. Plasma ctDNA is to be collected pre-dose as indicated in the Schedule of Assessments (Screening, Day 1 of Cycle  $\geq 2$  and EOT). [REDACTED]

25. Subjects will provide archived FFPE samples (collected within 5 years) for KRASG12C mutation confirmation that enables KRASG12C testing prior to starting all other screening procedures.
26. Testing for HIV, Hep B and Hep C should be conducted during Screening for eligibility determination. A positive HBsAg will be considered positive for Hep B. A positive anti-HCV antibody and anti-HIV antibody will be considered positive for Hep C and HIV, respectively. [REDACTED]  
[REDACTED]

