#### 3.2 Phase 1 Endpoints

##### 3.2.1 Primary Endpoints

- Type, incidence, severity (graded by NCI CTCAE, v5.0), attribution and timing of AEs
- Incidence of DLTs

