#### **4.2.2 Dose-limiting toxicity evaluation**

The DLT evaluation period is the first cycle of treatment and starts from treatment cycle 1/Day 1. If a subject is not evaluable for DLT due to reasons other than treatment-related toxicities in treatment cycle 1, then an additional subject will be enrolled in the cohort for replacement.

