## **8 ADVERSE EVENT REPORTING**

### **8.1 Adverse events**

#### **8.1.1 Definition of Adverse Events**

An AE is any untoward medical occurrence in a study subject administered a product; the event need not necessarily have a causal relationship with the treatment or usage. An AE can therefore be any unfavorable and unintended sign (including an abnormal laboratory finding), symptom, or disease temporally associated with the use of an investigational product, whether or not considered related to the investigational product.

The time period for collecting AEs for each subject begins from the time the subject provides written informed consent, until the end of safety follow-up (30 calendar days after the last administration of investigational product or until the start of other anti-tumor therapy (see Section 8.2.4 for details).

Examples of AEs include but are not limited to:

- Aggravation of existing (prior to enrollment of study) medical conditions/ diseases (including exacerbation of symptoms, signs, laboratory abnormalities);
- Any new occurrence of AEs: any adverse medical conditions that newly occur (including symptoms, signs, newly diagnosed diseases);
- Abnormal laboratory test findings of clinical significance.

All AEs should be recorded in the AE page of the eCRF in details, including: event term, start and stop date, severity, seriousness, the causal relationship between the event and investigational drugs, actions taken with investigational product, as well as final results and outcomes.

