### **8.2.3 Disease Progression and Death**

Disease progression (PD) is defined as that the disease under study is progressing or worsening, including radiological progression and progression of clinical symptoms and signs. New metastases relative to the primary tumor and the progression of the original metastases are both considered to be PD. Events that are life-threatening, requiring inpatient hospitalization or prolongation of existing hospitalization, resulting in persistent or significant disability/incapacity,

due to symptoms and signs of PD, should not be reported as an SAE. If there is any uncertainty about whether an SAE is caused by PD, it should be reported as an SAE.

In the study population of this trial, “disease progression” is an expected situation and shall not be documented as AE. When disease progression occurs, events used to confirm disease progression shall be reported as AEs. For example, in patients with epilepsy which are determined to be related to brain metastases, the AE term “epilepsy” rather than “disease progression” or “brain metastasis” shall be documented.

All cases of death that occur within 30 calendar days after the last administration of investigational product must be reported as SAEs, regardless of whether it is assessed by the investigator as likely due to disease progression, or the subject has received any other anti-tumor therapy. The term “death” should not be reported as an SAE term, but rather as an outcome of an event. The cause of death, medical conditions/disease (including exacerbation of symptoms, signs) should be used to be recorded in the eCRF and reported as SAEs. If the cause of death is unknown at the time of report, it should be recorded as “unknown cause of death”.

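### The ±7-day window on the Phase 1 safety follow-up visit lets the last scheduled AE review fall on day 23 of a 30-day collection period; Phase 2 uses +7

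*Protocol*

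**What the plan says.** Table 1-1 (Phase 1a) places the safety follow-up visit under the heading "Safety (30 days after last dose") with a window of ±7 days. Table 1-2 (Phase 1b) gives the same visit the same window. In Tables 1-3 and 1-4 (Phase 2, Arms B and F) the window for this visit is +7.

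Section 8.1.1 collects AEs from consent "until the end of safety follow-up (30 calendar days after the last administration of investigational product", or until other anti-tumor therapy starts. Section 8.2.3 adds: "All cases of death that occur within 30 calendar days after the last administration of investigational product must be reported as SAEs".

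Section 3.2.1 lists as a Phase 1 primary endpoint: "Type, incidence, severity (graded by NCI CTCAE, v5.0), attribution and timing of AEs". The other Phase 1 primary endpoint is DLT incidence, and section 4.2.2 states: "The DLT evaluation period is the first cycle of treatment".

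On the contacts around this visit, a note to Table 1-1 says of the end-of-treatment visit: "These visits need to be completed within 7 days of the last dose of study intervention". For Phase 2, a note to Table 1-3 says: "Subjects will be followed for survival status monthly". The Phase 1 tables have no survival follow-up column.

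**The concern.** Day 30 is both the nominal day of the visit and the last day of the collection period, so this visit is the one that closes the period. A symmetric window allows it to happen before the period is over. An event that begins after an early visit then depends on the subject volunteering it or on the site learning of it by chance.

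This matters more in Phase 1 than elsewhere. AE incidence and timing are primary there, yet Phase 1 has the looser end-of-period check. Phase 2, where safety is secondary, has a window that cannot close early and monthly survival contact behind it. No analysis can later recover events that nobody asked about.

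**Working it through.** **Inputs**
- Nominal visit: day 30 after last dose (all four schedule tables).
- Window: ±7 days in Tables 1-1 and 1-2; +7 days in Tables 1-3 and 1-4.
- AE collection and death reporting: to day 30 (sections 8.1.1 and 8.2.3).

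**Permitted visit days**
- Phase 1: 30 − 7 = 23 to 30 + 7 = 37.
- Phase 2: 30 to 30 + 7 = 37.

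The nominal day equals the stated period, so the plan's own figure of 30 days is reproduced. Only the lower end of the Phase 1 window departs from it.

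**Longest stretch without a scheduled check**
- Phase 1: 30 − 23 = 7 days (days 24 to 30), and 7/30 = 23.3% of the post-dose period.
- Phase 2: 30 − 30 = 0 days.

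**Whether another scheduled contact covers days 24 to 30**
- The end-of-treatment visit is due within 7 days of last dose, so it is too early.
- In Table 1-1 the last mark in the AE/SAE review row is in the safety column; the PFS column has none. The row labels in the lower part of Table 1-2 are not legible in the public copy, but section 7.1.9 covers Phase 1 follow-up as a whole and names no further AE visit day.
- PFS follow-up in Phase 1 takes place about every 12 weeks, only in subjects without progression, and stops at the start of another anticancer therapy. A subject who stopped for progression has no later visit.
- Monthly survival contact exists only in Phase 2.

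**Illustration of size**

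The protocol gives no post-treatment AE rate, so the following is an assumption. Let q be the 30-day risk of a first new AE after last dose, with constant hazard h = −ln(1 − q)/30. For a subject seen on day 23, the probability that this AE begins after the visit and by day 30 is exp(−23h) − exp(−30h). Dividing by q gives the share of such AEs with onset after the visit.

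| q | Probability of onset on days 24–30 | Share of first new AEs |
|---|---|---|
| 0.10 | 0.0224 | 22% |
| 0.30 | 0.0607 | 20% |
| 0.50 | 0.0878 | 18% |

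These are worst-case shares for a visit at the very start of the window. They show what the scheduled check would not see, not what would go unreported. An average over subjects would need the distribution of actual visit days, which the protocol does not give.

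**With a +7 window**, the earliest Phase 1 visit is day 30, the latest stays at day 37, and the uncovered stretch falls from up to 7 days to 0.

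**The case against.** A visit window says when a visit may take place; it does not alter the collection period. Section 8.1.1 fixes 30 calendar days for the whole study. Deaths within 30 days are reportable whatever the cause and whatever therapy follows (sections 8.2.3 and 8.2.4), and SAEs after follow-up are still to be reported if the investigator learns of them (section 8.2.5). An AE on day 27 therefore remains reportable after a day-23 visit. This stands. A reader might infer that the Phase 1 safety period is cut to 23 days, or that the two phases have different safety periods. The text supports neither: only the visit windows differ.

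Subjects without progression do come back for tumor assessment, and section 8.5 asks the investigator to assess new AEs at every study visit. This also stands. It would be wrong to say that Phase 1 has no later contact at all. The gap is confined to subjects with no later visit.

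General AE collection stops when other anti-tumor therapy starts; after that only drug-related SAEs are recorded, and deaths are still reported. For subjects who progress and move quickly to another treatment, the exposed stretch is shorter than 7 days or absent. This reduces the size but does not close the gap for the rest.

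A reader might also infer that the MTD or the recommended dose is at risk. It is not: DLTs are assessed in cycle 1, and AEs during treatment are reviewed at every scheduled treatment visit.

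What the objection does not answer is why the visit that closes a fixed 30-day period may precede its end in the phase where AEs are primary, when the Phase 2 tables avoid this.

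**Conclusion.** The point holds as a minor inconsistency between schedule and collection period. In Phase 1 the last scheduled AE review may fall as early as day 23, leaving up to 7 of 30 post-dose days (23%) without a scheduled check for subjects with no later visit. The AE part of the Phase 1 primary endpoint can be under-ascertained at its tail.

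The day count follows directly from the tables and needs no assumption. The 18% to 22% illustration rests on a constant hazard and a day-23 visit. The 23% is a share of post-dose follow-up days. It should not be read as a share of AEs missed, because AEs are collected from consent through all treatment cycles and unscheduled reports still count. The window applies to about 67 planned subjects (27 in Phase 1a plus 40 in Phase 1b), but how many would be seen early, and how many of those have no later visit, cannot be determined from the protocol.

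**What to change.** In Tables 1-1 and 1-2, change the safety follow-up window from ±7 to +7 days, as in Tables 1-3 and 1-4. Add the note that Phase 2 already carries, allowing AE status and concomitant medication to be checked by telephone at this contact.

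No visit is added and the latest permitted day stays at 37. Sites lose the option of an early visit, which the telephone option largely offsets. The two tables must be amended; if the sponsor classes the change as substantial, section 12.5 requires regulatory authority and IRB approval before it takes effect. The benefit is limited to Phase 1 subjects who have not yet passed safety follow-up, so it is sensible to fold the edit into the next amendment made for other reasons.
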